## Secondary Endpoints

- Therapeutic efficiency and clinical outcome of the selected therapeutic concept for AV malformation treatment at 12, 24, 36 months after completion of invasive treatment:
- *Physician-reported* signs: general appearance (for example swelling, pulsation, ulceration, cardiovascular health issues, bleeding) and location-specific signs (for example extremity length discrepancy, physical impairment)
- Radiological assessment
  - Evaluation of the therapeutic response depending on imagine outcome:
    - MR-angiographically measured reduction of the size (volume) of the nidus of the AVM
    - Degree of AVM devascularization (modified from Cho et al 2006 and 2008)^21,22^ before treatment to both primary and secondary endpoints:
      - 100% devascularization
      - 76-99% devascularization
      - 50-75% devascularization
      - < 50% devascularization
- Concordance between clinical and imaging outcome
- Changes in patient photographs (only qualitative analysis with Likert scale)
- Identification of potential biomarkers (as of now: Angiopoetin-I, Angiopoetin-II, S-endoglin, TGF-beta, Integrin beta-3, Ephrin-B2, HGF, Angiostatin, Endostatin, Endothelin, bFGF, VEGF, IL-6, PDGF, S100A8/9, S100B, PROX1, NRP2, PIK3CA including circulating free DNA) for prediction of therapy response or/and disease progression in an exploratory manner. For this purpose, an additional blood sample of about 10 ml blood is obtained for the study. In case of a clinically required biopsy of the vascular malformation, obtained material may similarly be assessed for additional tissue biomarkers.
- Recurrence rates:
  - Clinical recurrence (reappearance or aggravation of symptoms or findings which were initially regressive)
  - Imaging recurrence (recurrent increase in size or reperfusion of the vascular malformation after initial regression, occurrence of newly perfused AVM not detected before)
  - Recurrence rates/Progression after initial partial versus after complete response
  - Recurrence rates depending on the kind of treatment, the type of embolic agent (in the case of sclerotherapy, embolization), and the initial clinical findings of vascular malformation (initial size or the initial severity of symptoms)
- Other local and systemic side effects at the follow-up visit

Therapeutic safety of the selected therapeutic concept for AV malformation treatment

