## Description of the procedures

Potential study participants are screened on an interdisciplinary basis according to the inclusion criteria through the participating centers. The screening includes laboratory analysis and pre-interventional imaging with US/CT/MRI to confirm the diagnosis and to identify possible treatment options, which are performed with the routine clinical workup. Furthermore, the exact size assessment of the initial extent of the vascular malformation (volumetric measurements, flow characteristics) is being performed based on the cross-sectional imaging data.

After detailed study information (orally and written) and informed consent, the patient is included in the study. The pre-therapeutic assessment is composed of the same subjective (SF-36v2/SF-10, VAS, Likert scale of severity of symptoms) and objective (general appearance and location-specific signs) surveys that are done during the follow-up appointments. Following interdisciplinary consensus, multimodal treatment is initiated

**Compression treatment** is considered as the baseline therapy for all vascular malformations. Patients are supplied with custom made compression garments (class II). Depending on severity of disease, permanent compression therapy may be applied or temporary compression may be considered sufficient.

**Embolization** is performed under general anesthesia following standard operating procedures. Access to the lesion will either be gained via a transarterial, transvenous or percutaneous route, or a combination of the latter. For transarterial or transvenous access is gained via a femoral or brachial access using a 5-8 French-sized catheter equipment. If additional percutaneous access is required lesion will be punctured under ultrasound guidance using a 20-21G needle. After contrast injection digital subtraction angiograms are acquired and subsequently embolization is performed under fluoroscopy guidance. Periprocedural anticoagulation is performed using unfractionated heparin in a weight-adapted manner. Periprocedural antibiosis is not applied routinely. Depending on the extent and morphology of the lesion multiple treatment sessions will be required in order to achieve complete/near-complete embolization. All agents used for embolization purposes are CE-marked.

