# Follow-up

Follow-up will be performed following a dedicated time line:

- In case of conservative therapy biannually for 36 months
- Before initiation of interventional therapy as well as before each cycle of interventional treatment
- After initiation of interventional therapy every 6 months
- After completion of interventional therapy follow-up is performed at 6 (primary endpoint), 12 , 24 and 36 months

A flowchart with the corresponding clinical, laboratory and radiological examinations is attached at page 24.

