# Statistics

Analysis of clinical patient data, QoL data and Biomarkeranalysis will be performed separated from each other in a blinded setting. The study has an exploratory focus. All statistical testing will be performed based on a significance level of α=5%. No adjustment for multiple testing is planned.

Standard descriptive statistics will be used when reporting the study data. For continuous data, distribution parameters (mean, standard deviation, minimum, median, and maximum) will be computed and for categorical data, frequency counts will be given. If needed, 95% confidence intervals will be specified.

For the primary study parameters (scores PCS and MCS from adult SF-36v2 quality of life questionnaires, as well as PHS and PSS from kids SF-10 questionnaires), paired t-tests will be calculated comparing the scores at baseline to the respective scores at 6 months after the end of treatment (for embolized patients) or at the 24 months FU (for patients with conservative or medical treatment).

All QoL scores and subscores, as well as patient and physician reported pain and symptom data will be tabulated by study visit. Where appropriate, such data will also be summarized for different patient subgroups (e.g., age group, Schobinger stage, study treatment, etc.)

Morbidity, Mortality, and recurrence rates will be compared for different patient subgroups using Chi Square or Fisher’s exact test.

Summary statistics for AVM nidus volume reduction will be presented stratified by clinical outcome, as well as by patient subgroups, as needed. Crosstabulations of AVM devascularization (100% / 76-99% /50-75% / < 50% devascularization) vs. different clinical outcomes will be presented.

A sample size of N=74 (for children and adults, respectively) achieves 80% power to detect a mean of paired differences of 5 with an estimated standard deviation of differences of 15 and with a significance level (alpha) of 0,05 using a two-sided paired t-test.

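### Recurrence is to be compared as a crude proportion with no stated horizon, although the schedule lets observation time and visit spacing vary with treatment and lesion extent

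*Protocol*

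**What the plan says.** The Statistics section puts morbidity, mortality and recurrence into one sentence: "recurrence rates will be compared for different patient subgroups using Chi Square" or Fisher's exact test. It attaches no horizon, time origin or at-risk set to recurrence. All tests are at the 5% level without multiplicity adjustment, and the study is described as exploratory.

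The Follow-up section sets two clocks:

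- Conservative track: "In case of conservative therapy biannually for 36 months".
- Interventional track during treatment: "After initiation of interventional therapy every 6 months".
- Interventional track afterwards: "After completion of interventional therapy follow-up is performed at 6 (primary endpoint), 12 , 24 and 36 months".

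No length is given for the treatment phase. Description of the procedures makes it depend on the lesion: "Depending on the extent and morphology of the lesion multiple treatment sessions will be required".

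Secondary Endpoints defines clinical recurrence as "reappearance or aggravation of symptoms or findings which were initially regressive". The imaging definition begins "Imaging recurrence (recurrent increase in size or reperfusion of the vascular malformation after initial regression" and continues "after initial regression, occurrence of newly perfused AVM not detected before". Recurrence is to be examined by kind of treatment, embolic agent, and initial size or severity, and also after partial versus complete initial response.

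**The concern.** Recurrence accumulates with time, so a crude proportion means the same thing in two groups only if both were observed equally long. Here total observation can vary with treatment track and lesion extent, which are among the factors by which recurrence is to be compared. Visit spacing also differs: 6-monthly throughout in the conservative track, but 12-monthly after month 12 in the post-completion schedule. Some patients may also be lost before 36 months, and a crude proportion has no proper place for them.

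A second, separate issue is who can recur. A patient whose signs never regressed cannot meet the clinical definition or the first two imaging criteria. If such patients stay in the denominator, a group with a poorer initial response appears to recur less.

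At stake are the comparisons of recurrence by treatment and embolic agent. With every test at 5% unadjusted, nothing offsets an inflated error rate.

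**Working it through.** **The plan's own figure.** The only calculation in the protocol is for quality of life: N = 74 in each age group, paired difference 5, SD of differences 15, two-sided alpha 0.05, 80% power. With d = 5/15 and the noncentral t distribution, the smallest n is 73 (power 80.2%), and n = 74 gives 80.8%. The figure reproduces. It does not concern recurrence, and 74 per group is borrowed below only as an illustrative size.

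**Inputs for recurrence.** The schedule and the test come from the protocol. These are assumptions: 36-month recurrence of 40% (range 20% to 60%), a constant hazard identical in both groups, the pairs of observation times, and group sizes of 74 v 74 or 37 v 37. The times 42, 48 and 60 months arise as 36 months after completion plus a treatment phase of 6, 12 or 24 months, if that phase is counted. The pair 24 v 36 represents one group observed for less than the planned time.

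**Step 1, expected proportions with no true difference.** The hazard is h = −ln(1 − 0.40)/36 and the proportion with recurrence by t months is p(t) = 1 − exp(−ht) = 1 − 0.6^(t/36). This gives:

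- p(24) = 28.9%
- p(36) = 40.0%
- p(42) = 44.9%
- p(48) = 49.4%
- p(60) = 57.3%

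**Step 2, rejection rate of the uncorrected chi-square test** (40,000 simulated trials per row, nominal 5%):

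| Observation (months) | 74 v 74, 40% | 74 v 74, range over 20% to 60% | 37 v 37, 40% |
|---|---|---|---|
| 36 v 36 | about 5% | about 5% | 4% |
| 36 v 42 | 10% | 7–11% | 7% |
| 36 v 48 | 22% | 13–27% | 12% |
| 36 v 60 | 59% | 34–68% | 31% |
| 24 v 36 | 30% | 17–44% | 17% |

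**Step 3, log-rank test in the same setting** (40%, 74 v 74, 2,000 trials per pair). For 36/36, 36/48, 36/60 and 24/36 months it rejects in 4% to 6%. These runs used exact event times, so they show that the test copes with unequal observation. They do not show that it copes with unequal visit spacing.

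**Step 4, denominator alone.** Assume equal observation, 40% recurrence among responders in both groups, 74 v 74, and all patients in the denominator:

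- Response 90% v 90%: 0.9 × 0.4 = 36% in both; rejection about 5%.
- Response 90% v 70%: 36% v 0.7 × 0.4 = 28%; rejection 18%.
- Response 90% v 50%: 36% v 0.5 × 0.4 = 20%; rejection 59%.

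The group that responds better looks worse, whatever the length of follow-up.

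**The case against.** The strongest reply is that both tracks are nominally planned for 36 months, and that Secondary Endpoints names 12, 24 and 36 months after completion of invasive treatment. A chi-square comparison at one of those points among fully followed patients is valid, as the 36 v 36 row confirms. This stands. What remains is that the Statistics section does not tie recurrence to such a point, and that a clock starting at completion of invasive treatment has no counterpart in the conservative track.

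The reply also says that the figures are not the protocol's. That stands too: no passage states that treatment-phase time is counted, that a group will be observed for only 24 months, or that any recurrence subgroup has 74 patients. At 37 v 37 the inflation is about half as large.

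On the denominator, naming a test does not fix an analysis set. The natural reading of the clinical definition may already be a rate among patients who regressed, and the partial-versus-complete comparison contains only responders. A statistical analysis plan may settle this. The denominator point is therefore a conditional warning.

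A reader might also infer that only patients with initial regression can recur. The protocol does not support that: the last imaging criterion, newly perfused AVM, needs no prior regression. Restricting the analysis to regressors without reporting that event separately would lose a protocol-defined outcome.

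**Conclusion.** The point holds in a limited form. The protocol names a crude comparison of proportions for an outcome that accrues over time and sets no common horizon, while its schedule allows observation time and visit spacing to differ by factors it wants to compare. Where observation does differ, the false-positive rate can reach about 22% (36 v 48 months) or 30% (24 v 36 months) at 74 v 74, and about 12% for 36 v 48 at 37 v 37. These figures rest on an assumed 40% recurrence at 36 months and identical constant hazards.

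A reader might go further and conclude that follow-up is unequal by plan and the test therefore wrong as it stands, or that patients lost early are to be counted as free of recurrence. The protocol says neither. With complete follow-up to a common 36 months the test is sound.

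The consequence is moderate: recurrence is one of several secondary endpoints in an exploratory study, and the sample size does not depend on it. The change is still worth making, because a better-suited analysis is available at little cost.

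**What to change.** In the Statistics section, or in the statistical analysis plan:

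1. Define recurrence as time to first recurrence from a stated origin, in patients with documented regression, censored at the last assessment. The origin can be completion of invasive treatment or the visit at which regression is first documented; only the second exists in both tracks. If completion is used, patients whose regression is documented later should enter the risk set at that visit.
2. Give Kaplan-Meier or interval-censored estimates with 95% confidence intervals at 12, 24 and 36 months.
3. Compare groups by log-rank. Use interval-censored methods for conservative versus invasive treatment, because the visit grids differ and an ordinary log-rank on detection dates would carry that difference into the result. A comparison at one common fixed horizon, with censoring handled, is an acceptable alternative.
4. Report newly perfused AVM and progression in non-responders separately, so that neither is lost nor mixed into the denominator.
5. Keep chi-square or Fisher's exact test for outcomes with a common fixed window, such as peri-procedural morbidity.

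The cost is some added wording and slightly more analysis work. No visit, examination or sample size changes.

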# Study population

A total of 148 patients with AV malformations will be treated across centers, of which approximately 50 patients will be treated at LMU University Hospital Munich.

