## Inclusion Criteria

- Age: > 4 years, < 70 years
- Patients with simple peripheral (=extracranial) arteriovenous malformations according to the ISSVA (International Society for the Study of Vascular Anomalies) classification. Each patient and the corresponding diagnosis, is discussed in an interdisciplinary board for vascular anomalies before initiation of treatment.
- Patients with combined vascular malformations and arteriovenous malformations associated with other anomalies (e. g. Parkes Weber, PTEN hamartoma, HHT) according to the ISSVA (International Society for the Study of Vascular Anomalies) classification
- Patients with first line therapy or patients with previous alternative therapies in whom the previous treatments did not lead to durable symptom improvement
  - Previous surgery or embolization are not an exclusion criterion, but these patients will only be included in case of a therapy-free interval of 12 months
- Adults and children will be similarly included

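### The stated 80% power per age group needs about 74 complete pairs in each, but only 148 = 2 × 74 patients are to be treated, with no loss allowance, no secured age split and an unsettled primary population

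*Protocol*

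**What the plan says.** The Statistics section sizes the study by age group: "A sample size of N=74 (for children and adults, respectively) achieves 80% power to detect a mean of paired differences of 5". The SD of the differences is put at 15, and the calculation is made "with a significance level (alpha) of 0,05 using a two-sided paired t-test". The Study population section gives the overall number: "A total of 148 patients with AV malformations will be treated across centers". That is 2 × 74. The protocol gives no dropout rate, inflation or replacement rule.

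The age groups follow the questionnaire. Under Primary Endpoint, SF-10 is for ages 5–13 and SF-36v2 for those older than 13. Eligibility runs from over 4 to under 70 years. On the mix, the Inclusion Criteria say only: "Adults and children will be similarly included".

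Two sections differ on who supplies a primary observation. The Primary Endpoint section sets it 6 months after completed invasive treatment and names no other group. The Statistics section compares baseline with 6 months after end of treatment for embolised patients, "or at the 24 months FU (for patients with conservative or medical treatment").

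**The concern.** A paired t-test uses only patients with a score at both visits, so the N in its power formula is a number of complete pairs. The protocol carries that number over unchanged as the number of patients treated. Three conditions must then hold for the stated power to apply in both age groups:

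- Almost nobody is lost before a visit that comes 6 months after a treatment course often needing several sessions, or at 24 months without invasive treatment.
- Half of all patients fall in the 5–13 band, although eligibility extends to just under 70.
- Conservatively and medically treated patients count towards the 74, on which the two sections disagree.

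At stake is how a null result is read, above all in children. A reader relying on the Statistics section would credit each age group with 80% power for a 5-point change, when the evaluable pairs may support clearly less.

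**Working it through.** **Inputs from the protocol (Statistics):** mean paired difference 5, SD of differences 15, two-sided α = 0.05, 74 per age group. **From Study population:** 148 in total. **Assumed, because the protocol gives no figure:** loss of 10–30%; share of patients aged 5–13; share treated conservatively or medically.

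**Formula.** Exact power of the two-sided paired t-test with n pairs: noncentral t with n − 1 degrees of freedom and noncentrality (5/15) × √n, against the critical value t(0.975, n − 1).

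**Step 1: reproduce the plan's figure.** For n = 74 the noncentrality is 0.3333 × 8.602 = 2.867 and the critical value is 1.993.

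| Pairs | Power |
|---|---|
| 72 | 79.7% |
| 73 | 80.2% |
| 74 | 80.8% |

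The stated N is right. The smallest sufficient number is 73, so the margin is one pair per age group; losing two takes power below 80%.

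**Step 2: loss from 74 per group** (even age split, everyone counted, pairs rounded to the nearest whole number).

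| Assumed loss | Pairs | Power for 5 points | Change detectable at 80% power |
|---|---|---|---|
| 10% | 74 × 0.90 ≈ 67 | 76.7% | 5.2 |
| 20% | 74 × 0.80 ≈ 59 | 71.2% | 5.6 |
| 30% | 74 × 0.70 ≈ 52 | 65.5% | 5.9 |

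**Step 3: age mix of the 148, no loss.**

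| Assumed share aged 5–13 | Children | Power | Older patients | Power |
|---|---|---|---|---|
| 50% | 74 | 80.8% | 74 | 80.8% |
| 40% | 59 | 71.2% | 89 | 87.5% |
| 30% | 44 | 58.0% | 104 | 92.0% |
| 25% | 37 | 50.5% | 111 | 93.6% |

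With 37 children, the change detectable at 80% power is 7.1 points instead of 5. The older group gains what the children lose, but the 80% is claimed for both.

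**Step 4: who counts.** Pooled as in the Statistics section, conservatively and medically treated patients leave N at 74, at the price of mixing two visit times. If they fall outside the endpoint, as the Primary Endpoint section reads, or are tested separately, the invasively treated pairs are fewer. An assumed 10%, 20% or 30% of each 74 in that category leaves 67, 59 or 52 pairs, with the same power as in Step 2.

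**Step 5: sensitivity to the SD.** The Data scoring section puts SF-36v2 on a T-score scale with a general-population SD of 10. With SD s at both visits and correlation r, the SD of differences is s × √(2(1 − r)). Setting s = 10 and the result to 15 gives 225 = 200(1 − r), so r = −0.125, which looks cautious. Under assumed alternatives:

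- s = 10, r = 0.3: SD of differences 11.8; 52 pairs give 85%.
- s = 10, r = 0.5: SD of differences 10; 52 pairs give 94% and 37 pairs give 84%.
- s = 12, r = 0.3: SD of differences 14.2; most of the cushion is gone.

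**The case against.** The strongest reply is that nothing is miscalculated. The sample-size sentence is conditional and true: with 74 pairs, a difference of 5 and an SD of 15, power is 80%. A reader might infer an arithmetic error; there is none, and the figure reproduces.

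Second, every loss of power shown rests on rates that the protocol does not contain, and Step 5 suggests the planning SD may be generous enough to absorb a good part of the shortfall. This stands as far as it goes. The documents do not support the flat statement that the design fails to reach 80%, only that it does not secure it on the plan's own inputs. The protocol does not present the SD as a reserve for attrition, and the cushion shrinks if patients vary more than the general population.

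Third, 74 per group and a total of 148 together amount to an age target. That is a fair reading of intent, but the only sentence on the mix is an eligibility line without a number.

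Fourth, one might infer that the different visit times by themselves reduce N. They do not: they matter for N only if those patients are excluded or tested separately. The share may also be small, since the Exclusion Criteria remove patients with contraindications to invasive treatment or inaccessible lesions. What stands is that the two sections disagree on who counts.

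Finally, the study is declared exploratory, without multiplicity adjustment, and no decision rule depends on 80%. That lowers the weight of the point but does not make the stated power apply to the patients who will be evaluable.

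**Conclusion.** The point holds as a mismatch between the number treated and the number the power statement requires, not as an error in the formula. The stated 80% per age group survives the loss of one pair per group and no more, needs an even split by questionnaire that nothing in the protocol secures, and depends on a primary population that two sections define differently.

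At the plan's difference and SD, plausible but assumed losses of 10–30% bring power to between 76.7% and 65.5%. An assumed child share of one quarter brings it to 50.5% in children. The shortfalls would compound if they occurred together, and an SD of differences below 15 would offset them. The weight is moderate. It would be too strong to infer that the study is too small or must enrol more patients: in an exploratory study of a rare disease, an honest statement of the precision available is enough.

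**What to change.** Keep 148 and change the wording:

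1. State that 148 is the number of patients treated, not the number evaluable for the primary comparison.
2. Reconcile the Primary Endpoint and Statistics sections on which patients supply a primary pair and at which visit.
3. Give the expected evaluable pairs per instrument, with the assumed loss and age mix, and restate the power or detectable change for those numbers. For example, 59 pairs give 71% power for 5 points, or 80% power for 5.6 points, at an SD of 15. If a smaller SD is thought realistic, say so and show the result beside it.

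No extra patients are needed. An enrolment cap by age group is not required, and a cap at 74 would not cure attrition in any case. The cost is a few sentences and a less favourable stated power.
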